# A prospective, randomised, placebo-controlled, double-masked, three-armed, multicentre phase II/III trial for the Study of a Topical Treatment of Ischaemic Central Retinal Vein Occlusion to Prevent Neovascular Glaucoma – the STRONG study: study protocol for a randomised controlled trial

**DOI:** 10.1186/s13063-017-1861-3

**Published:** 2017-03-16

**Keywords:** Neovascular glaucoma, Neovascularisation, Ischaemic central retinal vein occlusion, Intraocular pressure, Aganirsen, Placebo, Topical treatment, Orphan disease

## Abstract

**Background:**

Neovascular glaucoma (NVG) is rare, comprising only 3.9% of all glaucoma cases. The most common cause of NVG is ischaemic central retinal vein occlusion (iCRVO). NVG frequently results in blindness and painful end-stage glaucomatous damage leading to the need for enucleation. Currently, there is no preventive therapy for NVG following iCRVO. Rescue treatments have severe drawbacks. Accordingly, there is a great need for preventing the often visually devastating outcomes of NVG. The STRONG study is designed to test whether the topically active anti-angiogenic agent aganirsen is able to inhibit the formation of neovascularisation leading to the development of secondary NVG in eyes with iCRVO. At the same time, STRONG will provide important information on the natural course of iCRVO and NVG in a large and well-characterised cohort of such patients.

**Methods/design:**

This protocol describes a phase II/III, prospective, randomised, placebo-controlled, double-masked, three-armed multicentre study for the investigation of aganirsen, a new topical treatment for iCRVO in order to prevent NVG. The study will evaluate the efficacy of two different doses of this newly developed antisense oligonucleotide formulated in an eye emulsion to avoid new vessel formation by blocking insulin receptor substrate-1 (IRS)-1. This leads to subsequent down-regulation of both angiogenic as well as proinflammatory growth factors such as vascular endothelial growth factor (VEGF) and tumour necrosis factor (TNF). Eligible patients (*n* = 333) will be treated with topical aganirsen or placebo for a period of 24 weeks. They will also be invited to participate in substudies involving analysis of gonioscopic images, detection of biomarkers for NVG and risk factors for iCRVO.

**Discussion:**

The STRONG study has the potential to offer a new treatment modality for patients suffering from iCRVO with a high risk of developing NVG. The topical administration can reduce patients’ burden and risk related to rescue treatment, such as destructive laser treatment or enucleation, but requires a high level of patient compliance.

**Trial registration:**

EudraCT: 2014-000239-18; ClinicalTrials.gov, ID: NCT02947867. (Registered on 15 October 2016); see also http://strong-nvg.com.

**Electronic supplementary material:**

The online version of this article (doi:10.1186/s13063-017-1861-3) contains supplementary material, which is available to authorized users.

## Background

Glaucoma is a group of conditions characterised by progressive optic nerve degeneration and loss of visual function, ultimately resulting in blindness. In contrast to very frequent types of glaucoma, secondary neovascular glaucoma (NVG) is rare at approximately 3.9% of all glaucoma cases. NVG is very aggressive, the prognosis is poor, and early, aggressive treatment is required to prevent blindness and painful end-stage glaucoma with irreversible loss of the eye. One common cause of NVG is ischaemic central retinal vein occlusion (iCRVO) [1–4]. iCRVO is a retinal pathology resulting in hypoxia, which leads to the expression of insulin receptor substrate-1 (IRS-1). IRS-1 in turn increases VEGF expression further along in the cascade [5] resulting in the pathogenic development of new vessels in the anterior and/or posterior segment of the eye. This new vessel formation can build an irreversible fibrovascular membrane over the trabecular meshwork and iris, leading to an obstruction of the trabecular meshwork and a clinically relevant increase in intraocular pressure (IOP) [4].

The study drug aganirsen is a 25-mer phosphorothioate antisense oligonucleotide of 8035 Da that inhibits new vessel formation by blocking IRS-1 and thus VEGF and tumour necrosis factor-alpha (TNF-alpha) [6, 7]. Aganirsen eye drops (saline solution) are safe at the maximum dose tested of 430 μg/day, which is equivalent to 10-fold and 5-fold the doses planned by the proposed study. Aganirsen eye drops have previously been shown in both phase II and III clinical trials to significantly inhibit corneal neovascularisation and to be well tolerated [8, 9]. Because the STRONG study planned by this consortium will be undertaken with a novel galenic formulation (emulsion) instead of saline eye drops, a comparative safety bridge study was performed for the two formulations (eye drops for corneal neovascularisation, and emulsion for prevention of NVG). No safety concerns occurred during the study.

Currently, reduction of IOP remains the focus of all therapeutic approaches for the majority of glaucoma patients, including those with NVG. For NVG, however, IOP-lowering medications are moderately helpful because outflow is obstructed and the accompanying inflammation and proliferative stimulus lead to the very poor success rate of fistulating glaucoma surgery. Currently, the common therapy for neovascularisation is pan-retinal photocoagulation (PRP), although additional anti-VEGF intravitreal injections have become more and more common for the therapy of neovascularisation. Thermic laser coagulation of the retina by PRP is strongly advocated and practiced widely for the management of iCRVO if new vessels have already formed [10, 11]. However, no definite guidelines exist regarding the exact indication and timing of PRP. As an alternative method of selective retinal ablation, pan-retinal cryotherapy may be performed on the peripheral fundus if the ocular media are too hazy for laser application.

There is a clear need to widen the existing therapeutic options for the treatment of iCRVO to prevent neovascularisation and NVG, with a specific focus on noninvasive therapeutic options aimed at prevention or early management respectively of the neovascular component of iCRVO. Hence, it is expected that aganirsen will benefit patients with iCRVO by interfering at an early stage in the neovascularisation process. Understanding the natural course of NVG, including biomarker and risk factor analysis, will further support the evaluation of new diagnostic and therapeutic interventions. These results could help to make early NVG diagnosis independently of an increased IOP by analysis of body fluids.

The primary objective of this multicentre randomised controlled study is to assess the efficacy and safety of aganirsen relative to placebo in preventing NVG in patients with iCRVO. We will evaluate the appearance of neovascularisation and the rise in IOP after 24 weeks (co-primary endpoint). We hypothesise that each of the two tested aganirsen doses will be superior to the placebo in preventing NVG at week 24. This study will also evaluate the effective dose of aganirsen.

The secondary objectives are to evaluate the efficacy of two aganirsen doses, to assess the aganirsen efficacy relative to placebo on time to, and intensity of, additional interventions, such as PRP or cryotherapy, to compare the effect of aganirsen and placebo on health outcome and quality of life (QoL) and to confirm a positive safety profile of aganirsen.

The aim of the imaging substudy is to develop an objective quantification of neovascularisation in the anterior part of the eye. For the biomarker substudy, the aim is to find possible biomarkers for iCRVO and NVG in tears and serum. The aim of the risk factor substudy is to identify potential novel risk factors for iCRVO and to evaluate if some of those parameters can be useful to differentiate patients who are at a higher risk of developing NVG.

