## Methods/design

Trial sponsor: Gene Signal SA, Genopole Biopark, Evry (Paris), France. Coordinating centre: University Medical Center at Johannes-Gutenberg University Mainz, Germany, Department of Ophthalmology. The study is funded by the European Commission 7th Framework Programme (Grant number 305321). This funding source had no role in the design of this study and will not have any role during its execution, analysis, data interpretation and dissemination of study results. The dissemination of study results is scheduled in a publication master plan and rights are organised in a consortium agreement. A Scientific Advisory Board and a Data Safety Monitoring Board will oversee the trial.

The STRONG trial is a phase II/III, prospective, 1:1:1 randomised, placebo-controlled, double-masked, three-armed multicentre trial for the study of the topical treatment of iCRVO to prevent NVG with a newly developed eye emulsion. It plans to enrol up to 333 patients suffering from a primary iCRVO or a conversion to iCRVO for no longer than 4 weeks in approximately 35 clinical sites in eight countries across Europe (Germany, France, Italy, Great Britain, Portugal, Spain and Hungary and Belgium; for a detailed list see www.strong-nvg.com). Trial staff will be trained and will follow standard operating procedures for the specific assessments and data collection. One eye per subject will be enrolled in the study. The study drug aganirsen will be administered as a topical emulsion in two different dosages and will be compared with a placebo group (Fig. 1).

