**Fig. 2 Fig2:**
[figure not shown]
Standard Protocol Items: Recommendations for Interventional Trials (SPIRIT) figure

The two study groups will be treated with aganirsen ‘low-dose’ (43 μg per day) or ‘high-dose’ (86 μg per day). The control group will receive placebo, as there is no labelled treatment for iCRVO to prevent NVG. The placebo is optically identical to the aganirsen emulsion.

Images of the anterior segment and gonioscopic photos of all patients participating in the STRONG study will be collected and evaluated for neovascularisation within the imaging substudy. Tears and serum samples will be collected during the biomarker substudy from 200 patients to evaluate possible markers for both iCRVO and NVG. The results will be compared with results of healthy subjects already available in a German database. Thirty-three eligible patients will be included in the risk factor substudy across all participating trial sites. At UMC Mainz, 33 age- and gender-matched healthy controls will be recruited. Blood samples will be collected to analyse laboratory parameters for coagulation and fibrinolysis and genetic factors to identify risk factors for iCRVO.

Protocol assistance at the European Medicines Agency (EMA) has taken place to define patients with a high risk for developing NVG. The inclusion criteria must be fulfilled at both the screening and baseline visits.

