### Statistics

Presentation of the sample size is based on both aganirsen doses combined demonstrating superiority placebo on the co-primary endpoints of neovascularisation and IOP at 24 weeks. Calculation of the sample size is based on the following: (1) An aganirsen to placebo ratio of 2:1, (2) Neovascularisation measured dichotomously (NVG = yes/NVG = no) with estimated disease rates in the population of 0.25 for aganirsen and 0.48 for placebo. Testing of neovascularisation will be done using the normal approximation to the chi-square distribution for consistency with O’Brien-Fleming Alpha spending, which is also computed based on normal approximation, (3) IOP measured dichotomously with estimated rates of events in the population of 0.24 for aganirsen and 0.41 for placebo at 24 weeks and (4) Up to four performed analyses. Based on albeit heterogeneous historical data, we estimate that 25% of subjects in the aganirsen group and 48% in the placebo group will develop NVG by 24 weeks. Given a 2:1 aganirsen to placebo assignment ratio, a total of 300 evaluable subjects – 200 with aganirsen and 100 with placebo – will provide 80% power to reject the null hypothesis that aganirsen is no better than placebo. Power computation is based on the chi-square test with a two-sided alpha = 0.05. Assuming that approximately 10% of subjects will not be evaluable due to loss to follow-up and other reasons, a total of 333 subjects are planned for this trial. Missing values of NVG and IOP will be imputed using the last observation carried forward (LOCF) method.

Primary efficacy will be assessed up to four times: two initial futility analyses, followed by an interim analysis for success/futility/continuation and a final analysis. The data will be summarised in tables listing the mean, standard deviation, minimum, median, maximum and number of subjects in a group for continuous data or in tables listing count and percentage for categorical data, where appropriate. Data listing by subject will be provided. The effects of noncompliance, dropouts and covariates, and their interactions with treatment will be assessed to determine the impact on the general applicability of results from this study. Secondary comparisons will be considered exploratory, so that there will be no Type I error adjustment for multiple secondary comparisons.

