### Co-primary efficacy I: NVG

The primary efficacy analysis will compare the proportion of subjects who developed NVG in the combined aganirsen arms versus in the placebo group. The analysis will test the following hypotheses: H0: P(NVG)_aganirsen_ ≥ P(NVG)_placebo_ and H1: P(NVG)_aganirsen_ < P(NVG)_placebo_, where P(NVG) is the proportion of subjects developing NVG by 24 weeks. The hypotheses will be tested using chi-square normal approximation. (‘Yes’: development of NVI, NVA, NVD and/or NVE, or rescue treatment and ‘No’: otherwise).

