### Secondary efficacy analysis

Aganirsen arms combined versus placebo: secondary analyses will be considered exploratory. Time to development of anterior neovascularisation will be compared by *t* test or Wilcoxon rank sum test (depending on distribution), since missing data will be imputed using LOCF and there will be no censored data.

Continuous change from baseline to week 24 parameters (e.g. size of retinal nonperfusion areas) will be assessed by analysis of covariance (ANCOVA), the covariate being a subject’s baseline variable, to prevent regression towards the mean. If the model shows a lack of fit, ANCOVA will be conducted on ranked data. The number of additional laser treatments will be compared between groups by Poisson regression.

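### The Background hypothesises that each dose beats placebo, but the planned tests compare aganirsen as one group with placebo, so a positive result would not confirm that hypothesis or show which dose works

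*Protocol article*

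**What the plan says.** **Aims (protocol article, Background).** The primary objective is the efficacy and safety of aganirsen relative to placebo, with no mention of dose. The hypothesis that follows is dose-specific: "We hypothesise that each of the two tested aganirsen doses will be superior to the placebo in preventing NVG at week 24". The next sentence reads "This study will also evaluate the effective dose of aganirsen". Dose returns among the secondary aims: "The secondary objectives are to evaluate the efficacy of two aganirsen doses".

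**Design (Methods/design).** The study is a "1:1:1 randomised, placebo-controlled, double-masked, three-armed multicentre trial" with doses of 43 and 86 μg per day.

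**Tests.**
- Statistics: "Presentation of the sample size is based on both aganirsen doses combined demonstrating superiority placebo on the co-primary endpoints". The allocation used for sizing is 2:1. Secondary comparisons are exploratory, without Type I error adjustment.
- Co-primary efficacy I: the analysis will "compare the proportion of subjects who developed NVG in the combined aganirsen arms versus in the placebo group".
- Co-primary efficacy II: the IOP hypotheses are written for a single aganirsen proportion against a single placebo proportion.
- Secondary efficacy analysis: "Aganirsen arms combined versus placebo: secondary analyses will be considered exploratory".
- Comparison by normal approximation to chi-square test: both co-primaries are tested at 240 subjects (two-sided 0.02442) and, if needed, at 300 (two-sided 0.04288).

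**The concern.** Rejecting the null for the two doses taken together shows that their average beats placebo. It does not show that both doses do, because an effective dose can carry an ineffective one. A reader who takes the Background hypothesis as the claim under test would draw a conclusion from a positive trial that the primary analysis does not support.

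The same reader would attach the stated 80% power to the dose-level hypothesis, although it was computed for 200 against 100 subjects. The aim of evaluating the effective dose has no efficacy test attached to it in the article. As the secondary analyses are described, any dose comparison would be exploratory and uncontrolled for error.

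**Working it through.** **Inputs (Statistics; Comparison by normal approximation to chi-square test).** NVG rates 0.48 placebo and 0.25 aganirsen; IOP failure rates 0.41 and 0.24; 300 evaluable subjects, so 100 per arm under 1:1:1; two-sided alpha 0.05 overall, 0.02442 at the interim, 0.04288 at the final analysis.

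**Formula.** Power = Φ[(|p1 − p2| − z·s0)/s1], with s0 = √[p̄(1 − p̄)(1/n1 + 1/n2)], s1 = √[p1(1 − p1)/n1 + p2(1 − p2)/n2], and p̄ the weighted mean rate. At alpha 0.04288, z = 2.025.

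**Step 1: the plan's own figure (100 placebo, 200 pooled aganirsen, alpha 0.04288).**
- NVG: p̄ = 0.327, s0 = 0.0574, s1 = 0.0586. (0.23 − 2.025 × 0.0574)/0.0586 = 1.94, power 97.4%.
- IOP: p̄ = 0.297, s0 = 0.0559, s1 = 0.0577. (0.17 − 2.025 × 0.0559)/0.0577 = 0.98, power 83.7%.
- Both, if independent: 0.974 × 0.837 = 81.5%. At alpha 0.05 the product is 83.3%.
- Enrolment: 300/0.9 = 333.3, against 333 stated.

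So 80% at 300 evaluable is reproduced for the pooled 2:1 comparison on both co-primaries.

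**Step 2: one dose against placebo (100 v 100, alpha 0.04288).** The article gives no dose-specific rates, so the assumption is that each dose has the planned aganirsen rate.
- NVG: s0 = 0.0681, s1 = 0.0661. (0.23 − 2.025 × 0.0681)/0.0661 = 1.39, power 91.8%.
- IOP: s0 = 0.0662, s1 = 0.0651. (0.17 − 2.025 × 0.0662)/0.0651 = 0.55, power 70.9%.
- Both, if independent: 0.918 × 0.709 = 65.1%.

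**Step 3: both doses, shared placebo arm, correlated endpoints (simulation).** Rescue treatment counts as failure in both co-primaries, so positive correlation is plausible. The article gives no value; a latent correlation of 0 to 0.8 is assumed. The sequential row stops the trial when the pooled test wins on both co-primaries at 240 subjects (80 per arm, alpha 0.02442) and then tests each dose at that same level. Otherwise the doses are tested at the final look after pooled success.

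| Setting | One dose | Both doses |
|---|---|---|
| NVG alone, final look | about 92% | 86–87% |
| Both co-primaries, final look only | about 65–70% | 49–55% |
| Both co-primaries, with the stop at 240 | about 50–57% (first dose tested) | 29–36% |

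The pooled comparison on both co-primaries at the final look has 82–83%. The stop at 240 occurs in about 62–66% of trials. Simulated figures vary by about one percentage point between runs.

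**Step 4: one dose inert, the other at planned rates (pooled test, alpha 0.04288).**
- NVG: pooled rate (0.48 + 0.25)/2 = 0.365; power about 45%.
- IOP: pooled rate (0.41 + 0.24)/2 = 0.325; power about 29%.
- Both: about 0.456 × 0.286 = 13% if independent, rising to about 21% at latent correlation 0.8.

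**The case against.** The strongest reply is that the primary objective says only aganirsen relative to placebo, which the pooled test answers. Dose efficacy is a secondary objective, and secondary comparisons are openly exploratory. On that view one sentence of the Background is out of step, and the unseen statistical analysis plan may contain dose-level tests. This stands in part: the pooled test does serve the primary objective, and the secondary objective does not restate the hypothesis that each dose is superior. But the article itself fixes the hypothesis, the comparison groups, the alphas and the power, and these disagree whatever another document adds.

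Three stronger readings are tempting and are not supported.
- **That the trial can say nothing about dose.** Allocation of 1:1:1 permits dose-level estimates, and the imaging substudy's comparison of exposure arms with placebo could be read as by dose. What is missing is confirmatory inference.
- **That the trial is underpowered for the hypothesis as worded.** That sentence names only NVG, where 100 per arm gives about 92% per dose and 86–87% for both. The fault there is the missing test; the shortfall appears when IOP is added.
- **That marketing authorisation requires evidence for a specific dose.** The Discussion says only that positive results would pave the way to authorisation. The documents state no such requirement, and this point does not rest on one.

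**Conclusion.** The hypothesis in the Background and the tests in the Statistics sections do not match. Followed as written, a positive trial supports aganirsen against placebo. It does not confirm that each dose works, and it does not show which one does. The 80% belongs to the pooled comparison on both co-primaries.

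A reader might infer that about 65–70% is the power to quote for a dose-level claim. That holds only if every trial reaches 300 subjects. With the planned success stop at 240, the figure is about 50–57% for the first dose tested and 29–36% for both.

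These sizes assume that both doses have the planned rates, 100 evaluable subjects per arm (80 at the interim), and a latent endpoint correlation of 0 to 0.8. The two futility looks were not modelled. The mismatch itself does not depend on any of these assumptions.

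**What to change.** Choose one of two options.

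**(a) Test the doses.** Keep the pooled test unchanged. After pooled success on both co-primaries, test one dose against placebo and then the other, each on both co-primaries and each with its own O'Brien-Fleming boundary. Fix the order before unmasking. State the dose-level power beside the 80%, including the figures that allow for the stop at 240.

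**(b) Reword.** Change the Background hypothesis to the pooled comparison, and label dose comparisons as exploratory estimates.

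In either case, report each dose against placebo with confidence intervals.

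**Cost.** Protocol and analysis-plan wording only; no extra patients and no extra alpha. The Trial status section says recruitment has not opened. Option (a) has two downsides. A less favourable power figure becomes visible. And if one dose is inert, the pooled gate on both co-primaries opens in only about 13–21% of trials at the final look, so the sequence adds little in that case. The sponsor should choose the testing structure with that in view.

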## Methods/design

Trial sponsor: Gene Signal SA, Genopole Biopark, Evry (Paris), France. Coordinating centre: University Medical Center at Johannes-Gutenberg University Mainz, Germany, Department of Ophthalmology. The study is funded by the European Commission 7th Framework Programme (Grant number 305321). This funding source had no role in the design of this study and will not have any role during its execution, analysis, data interpretation and dissemination of study results. The dissemination of study results is scheduled in a publication master plan and rights are organised in a consortium agreement. A Scientific Advisory Board and a Data Safety Monitoring Board will oversee the trial.

The STRONG trial is a phase II/III, prospective, 1:1:1 randomised, placebo-controlled, double-masked, three-armed multicentre trial for the study of the topical treatment of iCRVO to prevent NVG with a newly developed eye emulsion. It plans to enrol up to 333 patients suffering from a primary iCRVO or a conversion to iCRVO for no longer than 4 weeks in approximately 35 clinical sites in eight countries across Europe (Germany, France, Italy, Great Britain, Portugal, Spain and Hungary and Belgium; for a detailed list see www.strong-nvg.com). Trial staff will be trained and will follow standard operating procedures for the specific assessments and data collection. One eye per subject will be enrolled in the study. The study drug aganirsen will be administered as a topical emulsion in two different dosages and will be compared with a placebo group (Fig. 1).

